### Sample size calculation

Based on the results of other studies evaluating probiotic strains that will be used in the present study, we assume that the mean effect of intervention will be of a medium size. As the primary outcomes will be repeatedly measured and four groups of patients will be entering the trial, there will be an approximately 81% probability of correctly rejecting the null hypothesis of no difference between the study groups with a total of 116 patients.

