### Data management and analysis plan

#### Data analysis principles

To evaluate the efficacy of the intervention on the well-being of patients, the following changes from the baseline (V1) to the end of the study (V3) will be determined as primary outcomes:
The severity of depression symptoms:
MADRS total scoreBDI total scoreThe severity of psychopathological impairment:
SCL-90 total scoreThe quality of life:
SF-36 total scoreStress levels:
PSS-10 total score

To evaluate the effect of the intervention on physiological parameters [79], the following changes will be determined as secondary outcomes:
In serum, from the screening (V0) to the end of the study (V3), levels of:
proinflammatory biomarkers: hs-CRP, Il-6, Il-1beta, and TNF-alphagluten sensitivity biomarkers: anti-TG2 IgG antibodies and anti-AGA IgG/IgA antibodiesintestinal permeability biomarkers: I-FABP/FABP-2 and LBPmetabolism biomarkers: total cholesterol, LDL cholesterol, HDL cholesterol, TG, glucose, and insulinHPA axis biomarker: cortisolliver function biomarkers: ALT and ASTIn stool, from the baseline (V1) to the end of the study (V3):
taxonomic and functional analysis of gut bacterial communitySCFAs levelsBrain activity, from the baseline (V1) to the end of the study (V3):
EEG analysisGastrointestinal symptoms, from the baseline (V1) to the end of the study (V3):
GSRS scale.

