### Statistical analysis

Statistical analysis will be performed according to the E9 Statistical Principles for Clinical Trials [80]. For quantitative outcomes, the between-group comparisons will be performed using the ANOVA or Kruskal-Wallis rank-based nonparametric test depending on the data distribution followed by appropriate post-hoc tests. The qualitative outcomes will be compared using the Chi-square test. Longitudinal data will be analyzed with either repeated measures of ANOVA or aligned rank-transform ANOVA, depending on the data distribution, or McNemar’s test.

The analysis of the gut microbial community will include alpha diversity, beta diversity, ordination techniques (a principal coordinate analysis), and taxonomic and functional differences. Alpha diversity will be measured by means of the Chao1 (richness) and Shannon (richness and evenness) indices. All indices will be determined using originally observed count data (without data pre-processing) and comparison within the groups (V0–V3) and between the groups at the end of the study (at V3) using the non-parametric Wilcoxon signed-rank test or Mann-Whitney (or Kruskal-Wallis) test, respectively. Beta-diversity will be measured by means of the Bray-Curtis dissimilarity metric and the weighted UniFrac distance metric. Beta-diversity analysis will be preceded by the removal of rare species and normalization to account for unequal library sizes. The between-group differences in gut microbial composition will be visualized using principal coordinate analysis based on the Bray-Curtis dissimilarity and UniFrac distances. The permutational multivariate analysis of variance (PERMANOVA) will be conducted on the Bray-Curtis and weighted UniFrac dissimilarity matrices to assess the group-level (at V3) differences. Taxonomic differential abundance will be tested by comparing the fractional abundances. The analysis of alpha and beta diversity, ordination analysis, and taxonomic differential abundance will be conducted using the R (version 3.5.1) package Phyloseq [81]. The PERMANOVA+ add-on package of PRIMER 7 (version 7.0.13) will be used as analysis tools to compare beta diversity. To predict the metagenome functional content using the output of the 16S rRNA analysis pipeline, the software package PICRUSt will be used. Functional abundance differences will be analyzed and visualized using STAMP [82]. To account for multiple testing, FDR-adjusted *p* values (q values) will be reported.

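### Alpha diversity and PERMANOVA compare the arms at V3 only, although the stool outcomes are defined as changes and a pre-intervention stool sample is collected

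*Protocol article*

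**What the plan says.** Under Data analysis principles, the physiological measures are introduced with "the following changes will be determined as secondary outcomes". The stool items (bacterial community and short-chain fatty acids) are listed there as running from V1 to V3.

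Table 1 marks the stool sample at V0 (day –7 to –1, before randomisation) and at V3, not at V1.

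The Statistical analysis section then fixes the microbiome tests:

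- Alpha diversity (Chao1, Shannon): "comparison within the groups (V0–V3) and between the groups at the end of the study (at V3"), using Wilcoxon signed-rank within arms and Mann-Whitney or Kruskal-Wallis between arms.
- Beta diversity: PERMANOVA on the Bray-Curtis and weighted UniFrac "dissimilarity matrices to assess the group-level (at V3) differences".
- Taxonomic and functional abundance: tests are named, but no visit is given.

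The five primary scales are defined as change from V1 to V3. The general tests are ANOVA or Kruskal-Wallis, and "Longitudinal data will be analyzed with either repeated measures of ANOVA or aligned rank-transform ANOVA, depending on the data distribution". No baseline covariate is named.

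**The concern.** The outcome is a change and both samples needed to compute it are collected, yet the two between-arm microbiome tests that name a visit use only the second sample. The first sample enters the alpha-diversity analysis only through separate tests in each arm. Those tests do not compare randomised groups: time trends, regression to the mean and usual care act in every arm, and a significant result in one arm beside a non-significant one in another is not evidence that the arms differ.

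Two things are at stake. The planned test does not match the stated outcome, and a baseline measurement already paid for does not sharpen the arm comparison, in a trial with 30 patients per arm.

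**Working it through.** **1. The plan's own figure.** The article assumes a medium effect and reports about 81% power with 116 patients for four groups measured repeatedly. It gives no numerical effect size, correlation, number of measurements or alpha. Assume f = 0.25, correlation 0.5, m = 4 visits and alpha 0.05. For the group effect in a repeated-measures ANOVA:

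λ = f²·N·m / (1 + (m – 1)·0.5) = 0.0625 × 116 × 4 / 2.5 = 11.6, with 3 and 112 df, giving power 0.812.

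So the figure reproduces, and 116 is the smallest multiple of four that reaches 80% under these inputs. It describes a group effect averaged over four visits, two of them before the intervention, not the V1-to-V3 change. It was made for the primary scales. No figure is given for the stool outcomes.

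**2. Variance of the arm comparison.** Assume equal SD before and after (set to 1), correlation r, and a linear model:

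- V3 only: 1
- change score: 2(1 – r)
- V3 adjusted for baseline (ANCOVA): 1 – r²

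The saving of ANCOVA is r² against V3-only and 1 – (1 + r)/2 against change. The article gives no r, so a range is shown.

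| r | V3 only | Change | ANCOVA | Cut against V3-only | Cut against change |
|---|---|---|---|---|---|
| 0.3 | 1 | 1.40 | 0.91 | 9% | 35% |
| 0.5 | 1 | 1.00 | 0.75 | 25% | 25% |
| 0.7 | 1 | 0.60 | 0.51 | 49% | 15% |

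For the stool tests the relevant column is the cut against V3-only. At r = 0.2 it is only 4%. A plain change score is less precise than V3-only when r is below 0.5, so switching to change scores alone could lose precision. Adjustment avoids that.

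**3. Within-arm tests.** As an illustration, let all four arms have the same true standardised change d_z, with n = 30 and a paired t-test standing in for the Wilcoxon test. At d_z = 0.4 the power per arm is p = 0.563. The chance that the arms are neither all significant nor all non-significant is 1 – p⁴ – (1 – p)⁴ = 1 – 0.100 – 0.036 = 0.86. At d_z = 0.2, 0.6 and 0.8 it is 0.56, 0.38 and 0.05. Thus d_z = 0.4 lies close to the worst case (0.875 at p = 0.5). The size depends on d_z, but arms can disagree with no difference between them at any of these values.

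**4. Primary scales.** Four-group test, N = 116, assumed f = 0.25 on the V3 scale, so f²N = 7.25 and λ = 7.25 / variance:

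| r | λ, change | Power, change | λ, ANCOVA | Power, ANCOVA |
|---|---|---|---|---|
| 0.3 | 5.18 | 0.44 | 7.97 | 0.64 |
| 0.5 | 7.25 | 0.59 | 9.67 | 0.73 |
| 0.7 | 12.08 | 0.83 | 14.22 | 0.89 |

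The df are 3 and 112 for change, and 3 and 111 for ANCOVA.

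**The case against.** The strongest reply is that nothing here threatens validity. Arms were randomised, so a V3-only comparison is unbiased, and chance baseline differences are already covered by the test's error rate. This stands.

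Several stronger readings are tempting, but the article does not support them:

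- *All microbiome tests ignore baseline.* V3 is stated only for between-arm alpha diversity and PERMANOVA. Taxonomic and functional abundance have no stated visit, and short-chain fatty acids fall under the general tests, including the longitudinal ANOVA.
- *The primary analysis ignores baseline.* It does not: V1 enters through the change score or as a repeated response. Only a covariate is unnamed, and an analysis plan not shown could add one. The same applies to the handling of missed visits.
- *Within-arm results will be read as treatment effects.* The article does not say so, and it plans a direct between-arm test alongside them. The risk is one of interpretation.
- *The percentages apply directly to the planned tests.* They are linear-model results. For Mann-Whitney, Kruskal-Wallis and PERMANOVA they show direction and rough size only. Because r is unknown, the gain for the stool outcomes could be small.

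The core survives this. For alpha diversity and PERMANOVA the article names both the test and the visit, so this is a choice it has made, not detail left to another document.

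**Conclusion.** The point holds for alpha diversity and PERMANOVA. Neither planned arm comparison tests the change that defines the outcome, and the pre-intervention sample adds nothing to either. The loss is in efficiency and in the match between outcome and test, on secondary outcomes; it is not bias. Its size rests on an assumed correlation, equal variances and a linear model, and it ranges from modest at r = 0.3 to about half the variance at r = 0.7.

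For the primary scales there is no error, only an available improvement: a V1 covariate is more precise than a change score for any r below 1. The power figures for it also rest on the assumed f = 0.25 and alpha of 0.05.

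One contradiction has to be settled in any case: Data analysis principles puts the stool baseline at V1, whereas Table 1 and the Statistical analysis section put it at V0.

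**What to change.** 1. Reconcile the stool baseline visit across Data analysis principles, Table 1 and Statistical analysis. A V0 sample precedes randomisation, so it can serve as a covariate.
2. Alpha diversity: compare arms on the V3 index adjusted for the pre-treatment index, for example by ANCOVA, on ranks if needed.
3. Beta diversity: test arm differences in within-patient change, or an arm-by-time term using both samples. Permute arm labels across whole patients, keeping each patient's two samples together, because arm was randomised between patients. Permuting within patients would shuffle visits, not arms.
4. Label within-arm tests as descriptive.
5. As a further improvement, analyse the primary scales at V3 with the V1 score as covariate, or V2 and V3 in one mixed model with the same covariate.

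The cost is a little more analysis work. No new patients, visits or samples are needed.

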### Project Management

#### Timeline of the study

This study will consist of four visits (see Table 1 and the Methods of Assessment section for a detailed description of the framing and all procedures performed during each visit):
V0: Screening Visit to screen and enroll eligible patients into the study;V1: Baseline Visit up to 1 week after V0 to randomize patients to one of four arms of the study;V2: Visit 2, during the intervention period, after six weeks (±3 days) from Baseline Visit;V3: End of Study Visit to complete all procedures in this study, after 12 weeks (±3 days) from Baseline Visit.

The total duration from the screening to the end of the study will be 13 weeks at maximum.

#### Data safety monitoring

Based on anthropometric measurements, vital signs, and self-reported patient symptoms recorded at the visits during the intervention period (V2 and V3), the long-term safety and tolerability of probiotics and gluten elimination will be assessed. Participants will be asked to document any suspected adverse events in written form and to report them at the next visit.

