### Study population

A total of 120 adult volunteers with a diagnosis of major depressive disorder (MDD) will be recruited for this study. To be eligible in the trial, subjects must fulfil all of the inclusion criteria and none of the exclusion criteria, as stated below. The following inclusion criteria will be adopted:
Outpatients aged 18–60 years,Written informed consent to participate in this study before any study-mandated procedure,Meet the DSM-5 criteria for major depressive disorder (MDD) [42],Body mass index (BMI) ≥18.5 kg/m^2^ and ≤ 30 kg/m^2^,MADRS (Montgomery-Asberg Depression Scale) total score of 20 points or more (moderate or severe depression) at screening (V0) and at baseline (V1), andA willingness and motivation to follow the study protocol.

The exclusion criteria will be as follows:
Diagnosis of autoimmune, neurological, immunocompromised, thyroid, inflammatory bowel diseases, irritable bowel syndrome, diabetes, cancer, and/or IgE-dependent allergy;Psychiatric comorbidities (except specific personality disorder) including mental retardation, organic brain dysfunction, or addiction (except nicotine and caffeine);High risk of suicide in the investigator’s opinion;An infection one month before the study baseline visit (V1);The use of antibiotics and/or probiotics three months prior to the study;Glucocorticosteroids and/or metformin treatment;Dietary supplementation (except for vitamin D according to the “Vitamin D supplementation guidelines, 2018” [43]);Changes in a pharmacotherapy and/or psychotherapy of MDD 2 weeks before the trial entry;No specific (e.g. elimination, vegan, reduction) diet and changes in physical activity 4 weeks before the trial entry, andPregnancy or lactation.

Reasons for the participant to be discontinued from the study:
Withdrawal of informed consent,Lack or incomplete compliance with the diet and/or probiotic supplementation,Non-attendance at the study visits,Exclusion criteria found after enrollment, andAny serious adverse event during the intervention period (based on data safety monitoring).

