To the best of our knowledge, this will be the first intervention study assessing the efficacy of both probiotic supplementation and a gluten-free diet and comparing the effect of both interventions and their combination in MDD patients. The protocol and the outline were developed by a multidisciplinary researcher team. The methodology employed in the study benefited greatly from our diverse set of knowledge, experience and perspectives. Considering the highly rigoristic selection criteria, the participant group is relatively large. Rigorous procedures established for this trial will be followed by well-trained researchers to ensure that research will be conducted in accordance with standards of best practice. The measurements listed above will be introduced to reduce the potential bias related to confounding variables (e.g. smoking, physical activity, and diet).

There may be some possible limitations in the design of the study:

First, the impossibility of blinding the diet is a factor that could affect assessment of both the participant and investigator. For this reason, the researcher evaluating the severity of symptoms will not be informed as to whether the patient will be allocated to the GFD or GD arm of intervention.

Second, the lack of motivation is a symptom commonly experienced by MDD patients and could contribute to the non-attendance at the study visits, incomplete implementation of the intervention, or failure to complete the intervention.

Third, patients in the GFD groups receiving dietary advice might try to introduce other changes in food consumption (e.g. reduce the food portion size and/or consume more vegetables and fruits). Therefore, health improvement may not be specific to the implemented gluten-free diet.

Finally, recall bias in self-reporting is another potential confounder of the study. However, dietary consultation and food intake assessment during the study period should minimize the likelihood of its occurrence.

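### The stated basis for safety and tolerability is data from V2 and V3, so patients who stop before week 6 for a non-serious reason may contribute nothing, and discontinuation is not among the measures

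*Protocol article*

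**What the plan says.** The protocol article, under Data safety monitoring, names three inputs: body measurements, vital signs and symptoms that patients report. On the basis of these, "recorded at the visits during the intervention period (V2 and V3), the long-term safety and tolerability of probiotics and gluten elimination will be assessed". It adds one route for events between visits: "Participants will be asked to document any suspected adverse events in written form and to report them at the next visit".

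Two visits follow baseline. Timeline of the study gives "V2: Visit 2, during the intervention period, after six weeks (±3 days) from Baseline Visit" and "V3: End of Study Visit to complete all procedures in this study, after 12 weeks (±3 days) from Baseline Visit". Table 1 schedules the adverse events report at V1 (day 0), V2 and V3, with no contact between day 0 and V2.

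The Study population section has a list headed "Reasons for the participant to be discontinued from the study". Besides withdrawn consent, exclusion criteria found late and serious adverse events, it contains "Lack or incomplete compliance with the diet and/or probiotic supplementation" and "Non-attendance at the study visits". These reasons end participation in the study, not just in the treatment.

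The Discussion expects some losses. It says that the lack of motivation common in MDD "could contribute to the non-attendance at the study visits, incomplete implementation of the intervention, or failure to complete the intervention".

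**The concern.** Someone who finds the diet or the capsules hard to tolerate is likely to stop following them, stop attending or withdraw. Each of these is a reason to leave the study. If that happens before V2, the patient has no later visit at which to hand in adverse event notes or report symptoms. The fact of stopping, which is direct evidence on tolerability, is not on the stated list of measures. Followed literally, the text draws its conclusion from a group selected towards patients who could live with their regimen.

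The selection need not be equal between arms. Only the gluten-free groups change what they eat, so failure to follow the diet bears mainly on them. The Discussion says that positive results would support making dietary interventions an integral part of treatment in psychiatric wards. A tolerability statement that leans on attenders would be a weak support for that.

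**Working it through.** **Plan's own figure.** There is none on this point. The article gives no intolerance rate and no drop-out rate. Its one design figure, about 81% power with 116 patients, has no bearing here.

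**Who can go unseen, from the text alone.**

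- *Stops before V2 for a non-serious reason and does not return:* no V2 or V3 data and no next visit. Contributes nothing to the stated measures.
- *Found non-compliant at V2:* present at a visit where symptoms, vital signs and adverse events are recorded. Contributes V2 data.
- *Leaves between V2 and V3:* contributes V2 data. Anything that arose after V2 may be missed.
- *Leaves because of a serious adverse event:* the event is the recorded reason for leaving, so it is known.

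The gap is therefore mainly the first group.

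**Illustration of direction and possible size.** All rates below are assumptions. Let t be the true proportion intolerant and s the share of those patients who leave with nothing recorded. If all tolerant patients stay, the rate among attenders is

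t(1 − s) / (1 − t·s).

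For t = 0.20 and s = 0.50: 0.20 × 0.50 / (1 − 0.10) = 0.10 / 0.90 = 11.1%.

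| True rate t | s = 25% | s = 50% | s = 75% | s = 100% |
|---|---|---|---|---|
| 10% | 7.7% | 5.3% | 2.7% | 0% |
| 20% | 15.8% | 11.1% | 5.9% | 0% |
| 30% | 24.3% | 17.6% | 9.7% | 0% |

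The visible rate lies between about four fifths of the true rate and zero.

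**Between diets, same formula.** Assume 20% intolerant in the gluten-free arms and 5% in the others, a true difference of 15 points and a ratio of 4.0.

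| s | Gluten-free | Gluten-containing | Difference | Ratio |
|---|---|---|---|---|
| 30% | 0.14/0.94 = 14.9% | 0.035/0.985 = 3.6% | 11.3 points | 4.2 |
| 50% | 0.10/0.90 = 11.1% | 0.025/0.975 = 2.6% | 8.5 points | 4.3 |
| 80% | 0.04/0.84 = 4.8% | 0.01/0.96 = 1.0% | 3.7 points | 4.6 |

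The absolute difference shrinks. The ratio does not.

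**Relaxing one assumption.** The Discussion expects motivational drop-out, so tolerant patients will leave too. If a share r of them leaves, the rate among attenders is t(1 − s) / [t(1 − s) + (1 − t)(1 − r)]. With t = 0.20, s = 0.50 and r = 0.20 this is 0.10 / (0.10 + 0.64) = 13.5% rather than 11.1%. With r = s = 0.50 it is 0.10 / (0.10 + 0.40) = 20%, and the bias vanishes. The bias exists only to the extent that intolerant patients leave unrecorded more often than others.

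**The case against.** The strongest reply is that this reads an error into a condensed article. A reader might infer that leaving will go uncounted. No sentence says so, and a table of discontinuations by arm is something that an article commonly leaves to the full protocol or analysis plan. That stands against any claim that withdrawals will be ignored. It does not dispose of the point, because the Data safety monitoring section does not defer the choice: it states a basis, ties it to V2 and V3, and leaves discontinuation off it.

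A reader might also infer that tolerability will be judged only in patients who tolerated the intervention. The article does not support this either. Milder intolerance among attenders is recorded, and patients who leave after V2 have V2 data. Compliance is checked largely at or after visits: diet is assessed at V2 and V3, and blister packs are evaluated after the study. Serious events are known as a reason for leaving. The Discussion attributes losses to motivation, not to intolerance. All of this stands, and it narrows the gap mainly to non-serious stops before week 6.

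Two further points also hold. Tolerability is neither in the aim nor among the primary or secondary outcomes, and no comparison of tolerability between arms is announced, so the stakes are moderate. The listed discontinuation reasons contain no category for intolerance or for a non-serious adverse event, so a bare count of leavers would mix intolerance with motivational drop-out. That is a good reason not to make discontinuation the main measure. It is no reason to leave it out.

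**Conclusion.** The point holds as a limited one. As the article is written, a patient who stops before week 6 for a non-serious reason may add nothing to the tolerability assessment, and stopping is not among the stated measures. The likely direction is a picture that is too favourable, possibly more so in the gluten-free arms, because only they change their diet.

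The size cannot be derived from the document. The illustrative rates rest on assumed intolerance, an assumed share leaving unrecorded and, in the tables, no loss of tolerant patients. Equal loss of tolerant and intolerant patients would remove the bias. A reader might also infer that a real difference between arms will be hidden. The document does not support that: in the illustration the absolute difference narrows, but the gluten-free arms still show about four times the rate or more.

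**What to change.** In the Data safety monitoring section, state that safety and tolerability will be assessed by arm in all randomised patients who started the intervention. Report discontinuations by arm with the reason, noting intolerance or an adverse event where the patient gives it. Include adverse events known at discontinuation, whether or not V2 or V3 took place. Present these alongside the V2 and V3 symptoms and adverse events, not in place of them.

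The cost is a change of wording, a note of the patient's own reason at discontinuation, and one extra table. No visit is added and the stopping rules stay as they are. The downsides are that some reasons will be unknown or mixed with motivational drop-out, and that tolerability may look less favourable than under the present text.

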**Fig. 1 Fig1:**
[figure not shown]
Timeline of SANGUT STUDY visits. V0 – Screening visit; V1 – Baseline Visit; V2 – Visit 2; V3 – End of Study Visit

**Table 1 Tab1:** Schedule of study procedures

	Screening	Randomization	Intervention Period	End of the study
Visit Number	V0	V1	V2	V3
Visit time and Window	Day –7 to –1	Day 0	6 weeks ±3 days	12 weeks ±3 days
Informed consent	+			
Inclusion/exclusion criteria	+	+		
Somatic examination	+	+		
Neurological examination	+	+		
Socio-demographic characteristics	+			
Medical history	+			
Psychiatric history	+			
Depression symptoms severity	+	+	+	+
Stress level	+	+	+	+
Quality of life	+	+	+	+
Gastrointestinal symptoms	+	+	+	+
Dietary assessment	+	+	+	+
Physical activity	+	+	+	+
Anthropometric measures	+	+	+	+
Vital measures	+	+	+	+
Smoking status	+	+	+	+
Blood sample	+			+
Stool sample	+			+
Electroencephalography	+			+
Adverse events report		+	+	+

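### Participants are told to report any suspected adverse event at the next visit, with no exception for serious ones, although a serious event is a reason to discontinue the individual participant

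*Protocol article*

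**What the plan says.** Four places in the protocol article bear on this point.

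- **Data safety monitoring** gives the reporting instruction: "Participants will be asked to document any suspected adverse events in written form and to report them at the next visit". The same section says that, from data recorded at V2 and V3, "the long-term safety and tolerability of probiotics and gluten elimination will be assessed".
- **Study population**, in the list of reasons for discontinuing a participant, includes any "serious adverse event during the intervention period (based on data safety monitoring"). The words in the bracket are also the heading of the section that holds the reporting instruction. The same list includes "Non-attendance at the study visits".
- **Table 1 (Schedule of study procedures)** has a row "Adverse events report", marked at V1, V2 and V3. V1 is Day 0, the randomization visit.
- **Timeline of the study** lists four visits in all. V2 falls "after six weeks (±3 days) from Baseline Visit" and V3, the End of Study Visit, "after 12 weeks (±3 days) from Baseline Visit". No safety contact between visits is described.

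**The concern.** The instruction covers any suspected event, so on its face it covers serious ones, and it sets the time of reporting at the next visit. The discontinuation criterion is meant to act on serious events while the intervention is running. The information it is said to rest on arrives once in mid-course and once at the end. The two statements do not fit well together.

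The stake is patient safety. The participants are outpatients with a MADRS total of 20 or more at entry. High suicide risk is excluded at entry, and suicidal thoughts are an item of the MADRS, but the MADRS is rated only at visits. A participant who follows the printed instruction to the letter would bring a serious event, or new suicidal thoughts, to the team only at V2 or V3. The Discussion adds that low motivation "could contribute to the non-attendance at the study visits", so the next visit may itself be missed.

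**Working it through.** The article gives no figure for reporting delay, so there is nothing of its own to reproduce. The check is calendar arithmetic on the stated visit days.

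**Inputs** (Table 1 and Timeline of the study; the abstract for the length of the intervention)

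- V1 = Day 0. An adverse events report is marked here, but it precedes exposure to the intervention.
- V2 = 6 weeks ± 3 days = 42 ± 3, so Day 39 to Day 45.
- V3 = 12 weeks ± 3 days = 84 ± 3, so Day 81 to Day 87.
- Intervention = 12 weeks = 84 days.

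**Longest wait by the stated route.** This is the case of an event just after a visit, reported at the next one.

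- V1 to V2: nominal 42 − 0 = 42 days; longest 45 − 0 = 45 days.
- V2 to V3: nominal 84 − 42 = 42 days; longest 87 − 39 = 48 days; shortest interval 81 − 45 = 36 days.

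The 45 and the 48 cannot both apply to one participant. With V2 on Day 45, the longest wait after it is 87 − 45 = 42 days. With V2 on Day 39, the longest wait before it is 39 days. They are upper limits across participants.

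**Where the discontinuation criterion can act.**

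- An event between V1 and V2 is reported at V2, with about half of the intervention still ahead (84 − 42 = 42 days on the nominal schedule).
- An event after V2 is reported at V3. On the nominal schedule 84 − 84 = 0 days of intervention remain. At the earliest V3, 84 − 81 = 3 nominal days remain, but that visit is itself the end of the study.
- V2 is therefore the only visit at which this route leaves the criterion something to act on.
- The interval after V2 is 42/84 = 50% of the period from V1 to V3 on the nominal schedule. Across the windows it runs from 36/81 = 44% to 48/87 = 55%.

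**The texts side by side.** The discontinuation list separates out serious events and refers to safety monitoring. The safety monitoring section describes one reporting route for all events, by visit. Nothing in the article gives serious events a different route.

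**The case against.** The strongest reply is that a journal article condenses. The definition of a serious event, the reporting clock and the contact line normally sit in the full protocol and the consent form, and neither is shown. On this view the sentence describes the routine written log handed over at visits, and the discontinuation criterion acts whenever the team learns of an event. The link between the two rests on a phrase that matches a section heading; no sentence says that the criterion is applied only at V2 and V3. Nothing tells participants not to telephone.

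Much of this stands. It limits the claim to the route that the article states. It does not remove the point, because the article prints an instruction that covers any event and fixes its timing. If a faster route exists, the sentence misdescribes it; if none exists, the gap is real. Either way the sentence needs changing.

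A reader might infer more than the documents support:

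- **That a trial stopping rule is defeated.** The list concerns discontinuing an individual participant. It is not a rule for stopping the trial.
- **That participants would have to stay on capsules and diet until the next visit.** The instruction concerns recording and reporting. It says nothing about continued intake, and withdrawal of consent is not tied to a visit.
- **That a given number of exposure days is lost.** Such a figure would need assumptions about when events occur, that intake continues, and that the team has no other source of information. The article documents none of these.
- **That events in participants who miss a visit go unrecorded.** Non-attendance is expected and is a reason for discontinuation, but no text says that events in these participants are not collected.
- **That suicidality is unmonitored.** A psychiatrist rates the MADRS at the visits, and an exclusion criterion found after enrollment is also a reason to discontinue.

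**Conclusion.** The point holds as a fault in a stated instruction. As printed, a serious adverse event is reported at the next visit like any other. By that route the team may hear of it up to 45 days later between V1 and V2, or up to 48 days later between V2 and V3. For an event after V2, the participant-level criterion can act only at the End of Study Visit.

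The conclusion rests on reading *any* literally, on taking the bracketed words in the discontinuation list to mean the section of that name, and on the visit windows as given. The waits are upper limits for a participant who follows the instruction exactly and attends the next visit. The article gives no event rate, so no count of delayed events is offered. No efficacy estimate or primary outcome is affected. The case for change is patient safety at very low cost.

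**What to change.** Replace the reporting sentence under Data safety monitoring with wording such as: *Participants will keep a written record of suspected adverse events. They will contact the study clinic at once about any serious event (one that leads to hospital care or is life-threatening) and about new or worsening suicidal thoughts. All other events are reported at the following visit.*

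In the discontinuation list under Study population, state that the serious-adverse-event criterion is applied when the event becomes known, without waiting for V2 or V3.

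The cost is wording in two places and a clinic contact. There is one small downside: a caller may reveal the diet arm. The MADRS rater is to be kept unaware of allocation, so someone else on the team should take the contact.
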